## Methods/Design

### Trial design

The effect of Tai Chi Yunshou exercises for stroke patients will be assessed in a single-blind, cluster-randomized, parallel-controlled trial. Patients will be recruited from multicenter CHCs outpatient clinics. The protocol will be conducted at CHCs run by the Rehabilitation Hospital affiliated to Fujian University of Traditional Chinese Medicine (Fujian province, China), the First Affiliated Hospital of Henan University of TCM (Henan province, China) and the Second Affiliated Hospital of Shandong University of Traditional Chinese Medicine (Shandong province, China). Fujian University of Traditional Chinese Medicine (FJTCM) is responsible for training and supervising investigators in all research centers. A total of 10 community health centers (5 per arm) will be selected and randomly allocated into Tai Chi Yunshou exercise group or balance rehabilitation training group. Each community health centers will be asked to enroll 25 eligible patients into the trial. Primary and secondary outcomes will be measured at baseline and 4-weeks, 8-weeks, 12-weeks, 6-week follow-up , 12-week follow-up after randomization. A flow diagram of this trial is shown in Figure 1.

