### Outcome assessment

The variables in this trial consist of basic characteristic, primary outcome and secondary outcomes. The basic characteristic will be obtained at baseline (before intervention) via a questionnaire (Table 1). The primary and secondary outcomes consist of balance function, motor function, cardiopulmonary function, quality of life, and so on. All outcomes will be measured at baseline and 4-weeks, 8-weeks, 12-weeks, 6-week follow-up, and 12-week follow-up, respectively. Balance and proprioception tests, Cardiopulmonary function, three-dimensional gait analysis will be assessed by experienced operators at the Evaluation Department of Rehabilitation Hospital Affiliated to FJTCM. Other outcomes will be assessed by therapist in The Rehabilitation Hospital Affiliated to FJTCM, The First Affiliated Hospital of Henan University of TCM, and The Second Affiliated Hospital of Shandong University of Traditional Chinese Medicine. All outcome assessors or operators are blinded to the allocation results of participants. A summary of all measurements in this trial is shown in Tables 2 and 3.

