**Table 1 Tab1:** **Baseline descriptive data**

**Data**	**Content**
General data	CHC in which patients are recruited from, the date screening, patient’s address, name of accompanying, family members or the patient’s telephone number
Demographic data of subject	Gender, age, height ,weight, nationality, level of education and profession
Assessment of balance function before test	The ability to stand independently or with auxiliary, how many metres could walk with or without aids
Other	Previous treatment and duration of stroke, injury site of cerebrum, type of stroke and number of stroke

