### Primary outcome

Balance function will be assessed with BBS, which is identified as the most commonly used assessment tool across the continuum of stroke rehabilitation [31]. The Chinese version translated by Yan Tiebin and Jin Dongmei [32] will be used. The scale measures both static and dynamic aspects of balance though l4 items. Each item is scored from 0 to 4, with a score of 0 representing an inability to complete the task and a score of 4 representing independent item completion. A global score is calculated out of 56 possible points. A difference of 5.8 points on the BBS was required to conclude with 90% certainty that patients receiving stroke rehabilitation underwent a real change in balance [33].

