### Statistical analysis

The data will be analyzed at the patient level by a statistician working in the Center of Evidence-based Medicine of FJTCM, who is not involved in this trial. The primary analysis will compare the proportion of patients improved of balance function at the 12-week after treatment using a mixed-effects logistic regression model in the intention-to-treat sample (including all randomized patients). Treatment condition (intervention versus control) will be treated as a fixed effect. Baseline severity of balance dysfunction will be included as a covariate and variation among patient clusters (recruited by the same CHCs) will be modeled through random effects. Potential confounding for other measured cluster-level variables such as population size will be adjusted. Continuous outcomes will be analyzed according to the same scheme, but in linear rather than logistic regression models. Item-level missing data in psychometrically sound instruments will be treated in compliance with the corresponding manuals. If no recommendations are available, the expectation-maximization (EM) algorithm will be used to impute up to 30% of missing item responses. Unit-level missing data (patients not providing data for a whole measurement point due to dropping out of the study, for example) will be imputed via the EM algorithm using existing information from the baseline assessments. Further secondary analyses will include analyses in the per-protocol (completer) sample to test the robustness of the primary findings. No interim analysis is planned. Intervention-related data are stored and analyzed separately. All analyses will be implemented using SAS software (version 8.2, SAS Institute, Cary, NC, USA).

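### Read literally, the model adjusts the continuous secondary outcomes for baseline balance severity but not for their own baselines, which gives away precision

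*Protocol article*

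**What the plan says.** The Statistical analysis section sets out a mixed-effects logistic model for the primary comparison, with treatment as a fixed effect. Its patient-level adjustment is one sentence: "Baseline severity of balance dysfunction will be included as a covariate". For clustering, "variation among patient clusters (recruited by the same CHCs) will be modeled through random effects". The only other adjustment is at cluster level: "Potential confounding for other measured cluster-level variables such as population size will be adjusted". The rule for continuous outcomes follows: "Continuous outcomes will be analyzed according to the same scheme, but in linear rather than logistic regression models". The one change it states is linear for logistic; it mentions no outcome-specific baseline.

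Those baselines will exist. Under Outcome assessment: "All outcomes will be measured at baseline and 4-weeks, 8-weeks, 12-weeks, 6-week follow-up, and 12-week follow-up, respectively". Table 2 marks a pre-enrolment measurement for every secondary outcome, including the four (blood tests, proprioception, cardiopulmonary function, gait) that the tables measure less often afterwards.

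On the covariate itself, the Primary outcome section says "Balance function will be assessed with BBS", and the BBS is scheduled at baseline. Table 1, which lists descriptive baseline data, also has a row on balance before the test: "The ability to stand independently or with auxiliary, how many metres could walk with or without aids". The Statistical analysis section does not say which record supplies the severity covariate.

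**The concern.** The value of an outcome before treatment is usually its best single predictor after treatment. Baseline balance may serve well for a balance test, but it is likely to be a weak stand-in for baseline depression, quality of life or blood lipids. A model with balance severity alone leaves variation in the residual that the trial has already paid to measure.

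Few clusters make this more visible: "A total of 10 community health centers (5 per arm) will be selected and randomly allocated". With five centres per arm, moderate chance differences in baseline means are to be expected. Without the outcome's own baseline in the model, part of such a difference carries into the estimate of that particular trial. The Discussion relies on the secondary outcomes to describe benefits and risks broadly, so their precision matters.

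The unnamed instrument is a smaller matter, but the covariate also enters the primary model and should be identified there.

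**Working it through.** **Inputs from the article.** 10 CHCs, 5 per arm, 25 patients each (Trial design); intra-CHC correlation at most 0.05 (Sample size). Design effect: 1 + (25 − 1) × 0.05 = 2.2.

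**The plan's own figure.** The article gives no precision or power figure for a secondary outcome. Its BBS figure is 114 per group. With pooled SD √[(2.8² + 3.33²)/2] = 3.076, difference 2.0, two-sided 5% (sidedness assumed) and 90% power, the printed formula gives 49.72 × 2.2 = 109.4. A t-based version gives 51 × 2.2 = 112.2. Both are close to 114, and nothing below depends on it.

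**Assumptions (not in the article).** r = correlation of the outcome with its own baseline, 0.5 to 0.8; q = its correlation with baseline balance, 0.2 to 0.4; c = correlation between the two baselines. Correlations are taken as equal at patient and CHC level, so the design effect cancels from the comparison.

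**Step 1: raw follow-up scores.** The variance of the treatment effect is proportional to 1 − q² with baseline balance only and to 1 − r² with the own baseline. The reduction is 1 − (1 − r²)/(1 − q²):

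| r | q = 0.2 | q = 0.4 |
|---|---|---|
| 0.5 | 1 − 0.75/0.96 = 22% | 1 − 0.75/0.84 = 11% |
| 0.6 | 1 − 0.64/0.96 = 33% | 1 − 0.64/0.84 = 24% |
| 0.7 | 1 − 0.51/0.96 = 47% | 1 − 0.51/0.84 = 39% |
| 0.8 | 1 − 0.36/0.96 = 63% | 1 − 0.36/0.84 = 57% |

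In standard errors, the balance-only model is between √(0.84/0.75) = 1.06 and √(0.96/0.36) = 1.63 times as wide. Simulation of 10 clusters of 25 at intra-CHC correlation 0.05 (4,000 runs per setting) agrees: 1.13 at r = 0.5, q = 0.2; 1.37 at r = 0.7, q = 0.2; 1.61 at r = 0.8, q = 0.3. If q equals r there is no gain.

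**Step 2: change scores.** If follow-up minus baseline is analysed, the own baseline already enters by subtraction. With baseline balance as covariate the residual variance is 2(1 − r) − (q − c)², against 1 − r² with the own baseline. For q = 0.2 and c = 0.3:

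- r = 0.5: 0.99 against 0.75, a gain of 24%
- r = 0.6: 0.79 against 0.64, a gain of 19%
- r = 0.7: 0.59 against 0.51, a gain of 14%
- r = 0.8: 0.39 against 0.36, a gain of 8%

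From r = 0.6 upwards these gains are below those of Step 1, and far below at the top of the range. At r = 0.5 they are not smaller (24% against 22%).

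**Step 3: chance imbalance.** The difference in a baseline mean between arms has SD √(2/125 × 2.2) = 0.19 outcome SDs, a 95% range of ±0.37, and a probability of about 0.18 of exceeding 0.25. In the simulations, with raw scores, c from 0.3 to 0.6 and q up to 0.5, 29% to 69% of an own-baseline imbalance carried into the balance-only estimate, and about none once the own baseline was in the model. The average estimate under no effect was zero in every model. The imbalance is therefore one source of the wider standard error in Step 1, not an addition to it.

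**The case against.** The strongest reply is that this is a condensed article: covariates for each secondary outcome are commonly left to an analysis plan, and nothing here excludes own baselines. The phrase about the same scheme could even mean the baseline of whichever outcome is analysed. That stands as far as it goes: a reader might infer that own baselines are ruled out, and the text does not say so. But the article is not silent. It states a rule for all continuous outcomes and names the covariate, and an analysis plan that followed the rule literally would inherit the weaker model.

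A reader might also infer that the article defines baseline balance in two conflicting ways. It does not. The Table 1 items are descriptive and are never called severity, and the Primary outcome section ties balance to the BBS. The instrument is simply not named.

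Nor does the point reach every continuous outcome equally. If severity means the BBS, a continuous BBS analysis already has its own baseline. Timed-Up-and-Go and single leg stance are close to balance and should lose less.

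Finally, the size rests on assumed correlations, and the article sets no power target for secondary outcomes, so no power loss can be claimed against the plan. Its language of improvement may also point to change scores, for which Step 2 gives the gain. All of this limits the size of the point but not its direction.

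**Conclusion.** The point holds as a free improvement to a stated rule. It is not the correction of a bias. Read literally, the continuous secondary outcomes are adjusted for balance severity without their own baselines, which are collected. For outcomes that balance predicts weakly, such as depression, SF-36 and blood lipids, using the own baseline would cut variance by roughly 11% to 63% for raw scores, under own-baseline correlations of 0.5 to 0.8 and balance correlations of 0.2 to 0.4. For change scores the worked case gives roughly 8% to 24%. The article allows no firmer figure.

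Two stronger conclusions are tempting and not supported. One is that chance imbalance between five and five centres biases the secondary results; over randomisations it does not. The other is that imbalance is a second harm beside lost precision; it is the same loss seen in a single trial. The primary analysis is touched only in that its covariate should be named.

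**What to change.** In the Statistical analysis section, replace the covariate sentence and extend the rule for continuous outcomes along these lines:

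- The baseline BBS total score, as a continuous variable, is the severity covariate in the analysis of balance function.
- Each other continuous outcome is analysed in a linear mixed model with treatment, a random CHC effect and the baseline value of that same outcome. Baseline BBS may be kept in addition.

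This costs two sentences. No new data are needed, since Table 2 already schedules every baseline. The added covariate is at patient level, so unlike further cluster-level covariates it does not use up the few between-CHC degrees of freedom. Making the change before outcome data are examined also avoids a later choice of covariates that could look data-driven.

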### Sample size

The sample size calculation is based on a comparison between the intervention group and the control group, represented by the improvement of the Berg Balance Scale (BBS) as the main effect indicators. Our preliminary test data indicated that the means with standard deviation of the score with the intervention group was 8.5 points and 2.8 points, while 6.5 points and 3.33 points with the control group. The number of qualified participants recruited from each CHC will not be less than 25. And prior data indicate that the intra-CHC correlation coefficient is likely to be, at most, 0.05. One hundred and fourteen individuals per group are calculated according to the formula [26]:$$ n=\frac{2\left[{\left({\mu}_{\alpha }+{\mu}_{\beta}\right)}^2{\sigma}^2\right]}{\delta^2}\left[1+\left(m-1\right)\rho \right] $$with a type I error of 5% (α = 0.05) and 90% power (β = 0.10). Assuming a dropout rate of 10%, the sample size is 125 for each group and 250 in the two groups. Therefore, in order to achieve 80% power with an average cluster size of 25 patients and ICC of 0.05, 10 CHCs will be required (5 per arm).

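### Filling missed visits by EM from baseline data shrinks the treatment effect or, if arm is added to a single fill, understates its standard error; the week 4 and 8 BBS go unused

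*Protocol article*

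**What the plan says.** Under Statistical analysis, the primary comparison is the proportion of patients with improved balance at 12 weeks, "using a mixed-effects logistic regression model in the intention-to-treat sample (including all randomized patients"). Continuous outcomes follow the same scheme with linear models. On missing visits the section says: "Unit-level missing data (patients not providing data for a whole measurement point due to dropping out of the study, for example) will be imputed", and gives the method and its source: the values "will be imputed via the EM algorithm using existing information from the baseline assessments". It says nothing of multiple imputation or added variance, and does not mention arm, CHC or post-baseline scores as predictors.

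The one check on the main result that it names is this: "Further secondary analyses will include analyses in the per-protocol (completer) sample to test the robustness of the primary findings".

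Under Outcome assessment: "All outcomes will be measured at baseline and 4-weeks, 8-weeks, 12-weeks, 6-week follow-up, and 12-week follow-up, respectively". Table 2 confirms that BBS is scored at weeks 4 and 8. A patient who leaves after week 8 therefore has two post-baseline scores on the primary scale. The Sample size section allows for 10% dropout, about 25 of 250 patients.

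**The concern.** The text fixes both an algorithm and a source of information, so this is a stated method and not a detail left for later. Two problems follow, and which one applies depends on whether arm enters the imputation model.

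- **Arm left out.** Dropouts in both arms receive the same expected outcome for a given baseline, so the filled values carry no treatment difference and dilute the observed one.
- **Arm put in, one fill.** The estimate is no longer diluted, but predicted values are analysed as if measured. The spread between CHC means shrinks and the standard error is too small.

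On either reading the best available predictors of week 12 are set aside. If patients leave because of how they were doing at week 4 or 8, a model that sees only baseline cannot correct for it.

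**Working it through.** **Inputs.** From Sample size: "the score with the intervention group was 8.5 points and 2.8 points, while 6.5 points and 3.33 points with the control group", a difference of 2.0 points; 25 patients per CHC; ICC 0.05; 10 CHCs; 10% dropout; and the error rates "with a type I error of 5% (α = 0.05) and 90% power (β = 0.10"). Assumed, because the protocol does not give them: two-sided testing; correlation 0.3 between baseline and BBS change; correlations 0.6 and 0.8 of week 4 and week 8 change with week 12 change; 20% dropout as a second scenario.

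**The plan's own figure.** Pooled variance = (2.8² + 3.33²)/2 = 9.464, SD 3.076. Design effect = 1 + 24 × 0.05 = 2.2. The printed formula gives 2 × (1.960 + 1.282)² × 9.464/2.0² = 49.72, and 49.72 × 2.2 = 109.4. A t-based version gives 51 × 2.2 = 112.2. The protocol states 114, and 114 × 1.1 = 125.4, its 125 per group. This is close enough to use these inputs, and the point does not depend on the small gap.

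**Arm left out.** With equal, random dropout d, every dropout is filled on average with (8.5 + 6.5)/2 = 7.5.

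- d = 10%: 0.9 × 8.5 + 0.1 × 7.5 = 8.4; 0.9 × 6.5 + 0.1 × 7.5 = 6.6; difference 1.8.
- d = 20%: 8.3 and 6.7; difference 1.6.

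In general the effect becomes (1 − d) × 2.0, whatever the assumed correlations.

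**Arm put in, single fill.** Each CHC mean becomes roughly (1 − d) × its completers' mean + d × the arm mean. The arm difference is unchanged, but the spread between CHC means, which sets the reported standard error, is multiplied by about (1 − d). A 5% test on 8 degrees of freedom (critical value 2.306) then in effect uses 2.306 × 0.9 = 2.075 at 10% dropout, a type I error of 7.2%. At 20% it uses 2.306 × 0.8 = 1.845, or 10.2%. The normal approximation gives 7.8% and 11.7%.

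**Simulation.** 2,000 trials per scenario, 5 + 5 CHCs of 25, continuous BBS change, baseline-adjusted CHC means compared by t-test on 8 df, true effect 2.00. SE ratio is reported over true SE, over the runs with and without an effect; type I error comes from runs with no effect.

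| Dropout | Method | Estimate | SE ratio | Type I error |
|---|---|---|---|---|
| 10%, random | Baseline, no arm | 1.80 | 1.00–1.03 | 5.2% |
| 10%, random | Baseline + arm | 2.00 | 0.90–0.92 | 7.0% |
| 10%, random | Completers | 2.00 | 1.00–1.03 | 5.1% |
| 20%, random | Baseline, no arm | 1.60 | 1.01 | 5.0% |
| 20%, random | Baseline + arm | 2.00 | 0.81 | 10.6% |
| 20%, random | Completers | 2.00 | 1.01 | 5.1% |
| 10%, driven by week 8 BBS | Baseline, no arm | 1.73 | 0.98–1.02 | 4.4% |
| 10%, driven by week 8 BBS | Baseline + arm | 1.92 | 0.88–0.92 | 6.9% |
| 10%, driven by week 8 BBS | Completers | 1.92 | 0.98–1.02 | 4.6% |
| 18%, driven by week 8 BBS | Baseline, no arm | 1.51 | 0.99–1.02 | 4.4% |
| 18%, driven by week 8 BBS | Baseline + arm | 1.86 | 0.81–0.83 | 8.7% |
| 18%, driven by week 8 BBS | Completers | 1.86 | 0.98–1.02 | 4.6% |

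Other runs of the same design put the shortfall in SE at 10% dropout as high as about 15%. Adding arm and the week 4 and 8 BBS, even as a single fill, restored the estimate to 2.00 under both dropout mechanisms, with type I error of 5.0–5.8%.

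**Responder endpoint, illustration only.** Take 5.8 points as the cut-off and normal change scores. The true proportions are Φ(2.7/2.8) = 0.833 and Φ(0.7/3.33) = 0.583, a gap of 24.9 points. With arm left out, dropouts are classed as improved at the same rate in both arms, and the gap becomes 0.9 × 24.9 = 22.4 or 0.8 × 24.9 = 19.9. With arm in and correlation 0.3, the share of dropouts predicted above 5.8 is Φ(2.7/(0.3 × 2.8)) = 99.9% against Φ(0.7/(0.3 × 3.33)) = 76%. That gap is about 24 points, so the difference is hardly diluted.

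**The case against.** The strongest reply is that, read literally, the plan does no harm to the test. With arm left out, estimate and standard error shrink together: type I error stays near 5%, and power is about 86–87% at 10% dropout and 84% at 20%, the same as for completers. What remains is a conservative estimate, about 0.2 BBS points low at the planned dropout. The inflated error rate arises only if arm is added, which the text does not say. All of this stands, and the two harms are alternatives that must not be added together.

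It is also fair that neither single nor baseline-only appears in the text, and that an article may leave the number of imputations to a fuller document. Table 1 lists the recruiting CHC among the baseline data, so CHC, and through it arm, could be meant; that leads to the second reading. The text does name baseline as the source, so the unused interim BBS is the firmest part of the point.

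Two stronger readings are tempting, and the documents support neither. A reader might infer that the completer analysis is useless as a check. Under random or baseline-dependent dropout it is approximately unbiased with the correct size, and would on average expose the dilution. It shares the bias when dropout follows early response. A reader might also infer that nearly every dropout would be counted as improved. The Statistical analysis section defines no cut-off, the 5.8 under Primary outcome is a change-detection figure, and the inference fails at correlation 0.3 once arm is in the model. A weaker baseline predictor would be needed.

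**Conclusion.** The concern holds in moderate form and should be fixed. As most naturally read, the imputation rule shrinks the effect by about the dropout fraction (2.0 to about 1.8 at 10%, 1.6 at 20%) with type I error near 5%. With arm added to a single fill, the standard error is about 10–15% too small at 10% dropout and type I error is about 7–8%, rising to about 10% at 20%. Both versions discard the week 4 and 8 BBS. When dropout depended on week 8, that left a bias of 0.08 points at 10% and 0.14 at 18% even with arm included, and the completer analysis shared it.

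The (1 − d) dilution is algebra under random dropout that is equal in the two arms. The other figures rest on the assumed correlations and dropout models, and on an analysis of continuous BBS change by CHC means in place of the planned logistic model. The 20% rate is twice what the protocol expects. Effects on the responder endpoint are illustrative until improvement is defined.

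**What to change.** Replace EM imputation of whole visits. For the responder endpoint, use multiple imputation that includes arm, CHC, baseline BBS and all available interim BBS, derive improvement within each completed data set, and combine the results by Rubin's rules. Arm can enter as the A/B code described under Blinding, so the analyst need not be unblinded. For continuous BBS, use the same imputation, or a likelihood-based mixed model over baseline and weeks 4, 8 and 12 with CHC and patient random effects. Keep the completer analysis; a delta-adjusted sensitivity analysis is an optional addition.

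The cost is a change of wording and modest programming. The data are already scheduled for collection, and Trial status reports that recruitment was only starting. The standard error will be slightly larger than from a single fill that includes arm, because it then carries the imputation uncertainty.

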### Intervention group

The participants in the intervention group will accept a 12-week Tai Chi Yunshou exercises training with a frequency of 5 days per week and 60 minutes one day. The training scheme originated from the 24 forms simplified Tai Chi exercise, which is recommended as the popularity health sport by General Administration of Sport of China (Figure 2) [28,29]. Five qualified coaches who have engaged in the physical education over 5 years will teach the participants of correct Tai Chi Yunshou postures in CHCs during the whole intervention period. Each session included a 15 min warm-up time, then training 45 min continuously. The coach could adjust the length of the training time based on patients’ personal situation, and allocate properly. Individuals who have difficulty in completing the exercise continuously will be allowed to finish intermittently. But each session must last at least 15 min. All patients have 5 min to rest after training. One supervisors will be in charge of the management of training spot to guarantee the quality of Tai Chi Yunshou exercise training.

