### Follow-up

All participants will enter 12-week unsupervised follow-up period right after the end of intervention. Telephone follow-up will be performed once a week and home visits once a month. Throughout the follow-up period, patient’s current physical and mental status, rehabilitation exercises usage, the quality of life, compliance behavior and usage of drug will be recorded.

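### The completer analysis cannot test the robustness of the EM-imputed primary result, because both assume that dropout is ignorable given baseline

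*Protocol article*

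**What the plan says.** All statements are in the Protocol article, Statistical analysis. For the main comparison, the plan is to "compare the proportion of patients improved of balance function at the 12-week after treatment using a mixed-effects logistic regression model". Every randomised patient is included (intention to treat), with a random effect for community health centre (CHC). "Baseline severity of balance dysfunction will be included as a covariate".

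Unit-level missing data are described as "patients not providing data for a whole measurement point due to dropping out of the study, for example". Such data "will be imputed via the EM algorithm using existing information from the baseline assessments". The section does not say whether arm enters the imputation model. BBS is also measured at weeks 4 and 8 (Table 2), but the imputation as described uses baseline information only.

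The one analysis to which the section gives a robustness role is "analyses in the per-protocol (completer) sample to test the robustness of the primary findings". It does not define *completer*.

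**The concern.** A robustness check is useful if it can give a different answer when the assumption under test is wrong. The assumption at risk here is that patients who leave would have had the same outcome as those who stay, given baseline. The imputation builds that assumption in. The completer analysis, adjusted for the same kind of baseline information, makes it too.

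Participants and coaches know the allocation (Blinding section) and training lasts 12 weeks, so dropout related to poor progress in one arm is plausible. If it happened, the primary result could be biased and still be reported as robust because the completer result matched it. The label also invites readers to take a completer result as the effect in patients who followed the training, which completion alone does not establish.

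**Working it through.** **Inputs from the Sample size section.** BBS improvement 8.5 (SD 2.8) against 6.5 (SD 3.33); ICC 0.05; 25 per CHC; 10% dropout. So the difference is 2.0, the common SD is sqrt((2.8² + 3.33²)/2) = 3.076, and the design effect is 1 + 24 × 0.05 = 2.2.

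**The plan's own figure.** With two-sided 5% (sidedness assumed) and 90% power, n = 2 × (1.960 + 1.282)² × 3.076² / 2.0² = 49.7, and 49.7 × 2.2 = 109.4, so 110 per group. A t-based version gives 51 × 2.2 = 112.2, so 113. The stated 114 is close to the latter, so the inputs are usable.

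**Assumptions not in the protocol.** Correlation of baseline with change −0.4. Equal loss in both arms, 10% or 20%. Control loss is random. Tai Chi loss is either random or tied to poor gain, with logit slope 1 per SD of outcome. The calculation is large-sample, without clustering.

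**Arm in the imputation model.** Imputed values lie on the regression of outcome on arm and baseline fitted to completers. Adding points on a fitted plane does not change a least-squares fit, so the imputed estimate equals the completer estimate whatever caused the dropout.

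**Arm omitted.** Dropouts in both arms get the same prediction for a given baseline. The estimate becomes (1 − loss) × completer estimate, and the gap is loss × completer estimate.

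| Loss per arm | Tai Chi dropout | True | Completer | EM with arm | EM without arm |
|---|---|---|---|---|---|
| 10% | random | 2.00 | 2.00 | 2.00 | 0.9 × 2.00 = 1.80 |
| 10% | informative | 2.00 | 2.23 | 2.23 | 0.9 × 2.23 = 2.01 |
| 20% | random | 2.00 | 2.00 | 2.00 | 0.8 × 2.00 = 1.60 |
| 20% | informative | 2.00 | 2.45 | 2.45 | 0.8 × 2.45 = 1.96 |

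With arm, the gap is zero in every row. Without arm, it is 0.20 (random) against 0.22 (informative) at 10% loss, and 0.40 against 0.49 at 20%. It therefore mainly reflects the amount of loss.

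**Sensitivity.** With slope 2, the completer and EM-with-arm estimates are both 2.38 at 10% loss and both 2.68 at 20%. With the arm-specific SDs and an arm-by-baseline term in the imputation, slope 1 gives 2.20 and 2.21 at 10%, and 2.41 and 2.43 at 20%.

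**Binary outcome.** The protocol sets no cut for *improved*. The 5.8-point change quoted under Primary outcome is used here for illustration, with arm-specific SDs and slope 1.

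| Loss per arm | Measure | True | Completer | EM with arm | EM without arm |
|---|---|---|---|---|---|
| 10% | risk difference | 0.25 | 0.28 | 0.28 | 0.25 |
| 10% | log odds ratio | 1.39 | 1.62 | 1.74 | 1.51 |
| 20% | risk difference | 0.25 | 0.31 | 0.31 | 0.24 |
| 20% | log odds ratio | 1.41 | 1.84 | 2.11 | 1.62 |

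With arm in the model, both analyses move upward on both scales. They agree on the risk difference, and less closely on the odds-ratio scale that a logistic model reports.

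**The case against.** **The check can disagree.** Imputation "imputed via the EM algorithm using existing information from the baseline assessments" may well leave arm out, since arm is not a baseline assessment. With a real 2-point effect the two analyses then differ, for example 2.01 against 2.23. This stands: one cannot say that the analyses always agree. It does not rescue the check, because nearly the same gap appears when dropout is harmless (1.80 against 2.00).

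**The binary primary outcome behaves less neatly.** This also stands. The exact coincidence belongs to the mean BBS change, and the odds ratios agree only loosely.

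**The sizes rest on assumed mechanisms.** True. Of the dropout inputs, only the 10% loss is documented.

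**A completer analysis has a use, and the full analysis plan may add more.** It does show whether imputed values drive the result, and the list of secondary analyses is not stated to be exhaustive. But the article itself assigns this analysis the robustness role, and that assignment is what is poorly chosen.

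**Stronger readings that the documents do not support.** A reader might infer that non-adherent patients who attend the visit count as per protocol. *Completer* is undefined and could mean finishing the 12-week training. On that reading the numerical coincidence is not guaranteed, but the analysis still says nothing about unobserved outcomes. A reader might also note "The coach could adjust the length of the training time based on" the patient's situation and count shortened sessions as deviations, but an adjustment that the protocol permits is not a deviation. Finally, the Follow-up section says that "compliance behavior and usage of drug will be recorded", and Tables 2 and 3 have no attendance row. That does not show that attendance goes unrecorded during training. A register or an adherence threshold may be in the full protocol or analysis plan, so their absence is no part of this point.

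**Conclusion.** The point holds in this form: the completer comparison cannot test the missing-data assumption behind the EM-imputed primary result. With arm in the imputation model, the estimates of BBS change coincide while both are biased by about +0.2 points at 10% loss and +0.5 at 20%. That is roughly a tenth and a quarter of the planned 2-point difference. It assumes that poor responders leave one arm only, with logit slope 1 per SD. With arm omitted, the analyses differ by about 0.2 points at 10% loss whether or not dropout is informative, given the planned difference. On the binary primary outcome, with arm in the model, the bias has the same direction and the agreement is looser.

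This does not show that the trial's result will be biased. At the planned 10% loss the bias is modest under these assumptions. It shows that agreement between the two planned analyses would be weak evidence of robustness. The combined label also merges two different sets, completers and adherers.

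**What to change.** 1. Report the completer analysis under that name, as a limited supporting analysis. Do not label it per-protocol or cite its agreement with the primary result as evidence of robustness.
2. State whether arm is in the imputation model.
3. For robustness, add a delta-adjusted (pattern-mixture) analysis. Lower the imputed BBS values of dropouts in steps (for example 0 to 8 points), separately by arm. Apply the same definition of *improved*, refit the planned mixed-effects model with the CHC random effect, and report the shift at which the conclusion changes. On the mean scale, a shift of d in one arm moves the difference by loss × d. At 10% loss, a shift of 2.3 points would offset the 0.23-point bias shown above (0.10 × 2.3 = 0.23).

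The cost is a few extra model runs and some wording, with no new data. The robustness statement may also turn out less favourable.
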